## Abstract

**Introduction:**

Couple relationships are important for health. Relationship distress is associated with increased incident and prognostic cardiovascular risk, while positive support is linked to heart-healthy behaviors and improved outcomes. This paper describes the study rationale, objectives, design, and methods of the Healing Hearts Together (HHT) randomized controlled trial (RCT).

**Objectives:**

The primary objective is to examine the difference in relationship quality between the 8-week HHT intervention group and usual care (UC) at program completion. Secondary objectives include evaluating the impact of HHT on relationship quality at 6 months, and mental health, quality of life, and cardiovascular risk factors measured at 8 weeks and 6 months post-intervention, as compared to usual care.

**Methods:**

Patients and their partners are recruited within 6 months of a cardiac event, procedure, or hospitalization and randomized 1:1 to HHT or UC. Assessments occur at baseline, 8 weeks, and 6 months follow-up. Analyses are planned as intention-to-treat, with multi-level analyses of covariance (ANCOVA) for the primary outcome: 8-week relationship quality as measured by the Dyadic Adjustment Scale. Secondary objectives will be evaluated using multi-level modeling for repeated measures.

**Anticipated results:**

It is expected that participants randomized to HHT will report higher relationship quality and improved secondary outcomes than will participants in UC.

**Conclusion:**

As the first study to evaluate a relationship-enhancement program for couples with cardiac disease, findings will have important clinical implications regarding the effect of relationship interventions on heart health.

## Background

The quality of couple relationships significantly affects both psychological and physical health, particularly in the context of cardiovascular disease (CVD) (Azizi et al., 2024). High-quality relationships, characterized by satisfaction and minimal hostility, are linked to better health outcomes, whereas strained relationships or a sense of disconnection from close others can lead to adverse outcomes. To illustrate, a meta-analysis involving 35,925 participants reported that loneliness and social isolation increased the risk of coronary artery disease (CAD) by 29% (Valtorta et al., 2016). In contrast, positive support provided by a partner can protect against cardiac-related health issues, including metabolic syndrome and post-operative complications. For example, patients reporting satisfying relationships are 3 times more likely to be alive at 15 years post-bypass surgery (King and Reis, 2012).

Couples’ relationship quality (RQ) may influence heart health both directly and indirectly. Direct pathways include the impact of psychological and physical challenges on the cardiovascular, neuroendocrine, and immune systems. Psychological stress from relationship strain or hostility can activate the sympathetic nervous system, leading to increased blood pressure, heart rate, and cardiac output (Valtorta et al., 2016; Kelli et al., 2019). Supportive relationships, on the other hand, are linked to improved heart rate variability (HRV), a measure of the heart’s ability to respond to stress. Higher HRV is associated with better cardiovascular health (Goodyke et al., 2024) and lower stress hormone levels, reducing the risk of CAD and mortality (Pourmand et al., 2023). Further, couples in which one partner criticizes while the other shuts down emotionally secrete higher levels of cortisol during conflict. Elevated cortisol levels are strong predictors of CAD and cardiac mortality (Shrout et al., 2020).

Indirect pathways in which RQ influences heart health involve health behaviors driven by RQ (Azizi et al., 2024; Khaing et al., 2017; Rapelli et al., 2022; Bertoni et al., 2023). Relationship problems can lead to engagement in risky health behaviors such as smoking and alcohol use (Roberson et al., 2018), whereas better marital adjustment and positive dyadic coping is associated with enhanced medication compliance (Rapelli et al., 2022) and cardiac rehabilitation (CR) (Trevino et al., 1990). Spouses can exert social influence over health behaviors, such as preparing low-sodium meals, modeling healthy behavior (e.g., exercise), or assisting in the management of disease (e.g., medication management) (Ford et al., 2009). However, if this support is in the form of overprotection, for example, it may cause more harm than good (Bertoni et al., 2023). Satisfying relationships are associated with lower rates of mental health problems and better quality of life in cardiac patients, whereas discord can exacerbate anxiety and depression (Bouchard et al., 2021; Bouchard et al., 2023), increasing the risk of cardiac complications and death (Civieri et al., 2024).

Current cardiac interventions often overlook the importance of RQ. Consequently, few studies exist that measure the effect of couples-based interventions in patients with heart disease and their partners. Existing research has focused on traditional approaches such as diet, exercise, and stress management, producing inconsistent results. A recent scoping review (Rapelli et al., 2023) of couple-based psychological interventions for cardiac patients and their partners identified 11 studies (6 RCTs). Many interventions were classified as “partner-assisted” (i.e., partners complete tasks to help the patient), with the remaining studies being “couple-interaction” interventions in which couple adjustment and coping were addressed (Gartner et al., 1988; Lenz and Perkins, 2000; Sher et al., 2014; Stewart et al., 2001). Of the latter studies (3 RCTs), the interventions showed little improvement over control conditions. Gartner et al. (1988) reported increased patient tolerance for emotional distress at 3 months post surgery, but no differences were found at 6 months, and no partner effects were observed. An enhanced version of this intervention did not produce differences between intervention and control groups (Lenz and Perkins, 2000). Lastly, compared to a patient-only education program for cardiac risk reduction, couples receiving education plus counseling on communication skills and relationship issues reported higher levels of physical activity, but no differences were detected on any of the other variables of interest (e.g., body mass index, nutrition, medication compliance) (Sher et al., 2014). As such, there has been a call in the literature for high-quality, contemporary studies of couples facing heart disease that includes enhanced relationship-focused interventions and measures of RQ for the patient and partner to enhance intervention success (Rapelli et al., 2023; Pietromonaco and Collins, 2017; Pietromonaco et al., 2013; Smith, 2022). The inclusion of partners in the care of patients with CVD has the potential to not only enhance patient outcomes, but also to help partners who often share similar cardiovascular risk factors.

With its solid foundation of evidence (Mikulincer and Shaver, 2016; Cassidy and Shaver, 2016) relationship scientists have applied attachment theory to understand the link between RQ and health, as well as to address the role of relationship distress in the health context. Attachment theory specifies that all human beings have an innate need for emotional connections with significant others and, when these ties are threatened (e.g., during a cardiac event), immense distress is triggered and attachment behaviors (e.g., seeking closeness) as well as caregiving behaviors (e.g., protection) are activated in an attempt to gain reassurance and/or emotional homeostasis. Emotionally focused, attachment-based interventions have been applied to help couples solidify a sense of security and connection by articulating and reaching out when feeling vulnerable (e.g., “what would I do if you died?”). These interventions have produced improved relationship satisfaction and health outcomes (e.g., reduce heart rate and cortisol levels) during stressful situations (Greenberg and Watson, 2006; Johnson, 2019; Johnson and Denton, 2002).

In the cardiac context, members of our team created the *Healing Hearts Together* (HHT) program, adapted from the *Hold Me Tight: Conversations for Connection* program (Johnson, 2010). Rooted in attachment theory, HHT emphasizes the need for close emotional bonds between partners and introduces strategies to address the emotional challenges of heart disease to promote healthy coping (Tulloch et al., 2021). Our proof-of-concept data demonstrated clinically significant improvements from pre- to post-intervention on relationship distress, depression, anxiety and quality of life (Tulloch et al., 2021) among patients with heart disease and their partners. However, no lifestyle, physiological (e.g., inflammatory makers, cortisol reactivity), or cardiovascular risk factors or outcomes were measured, and a comparison group was not included. Further study is needed to definitively determine the clinical impact and underlying mechanisms of HHT.

## Study aims and objectives

The primary aim of this RCT is to examine the efficacy of the 8-week HHT program on the relationship quality of patients with CVD and their romantic partners at 8 weeks, in comparison to UC. We expect that those assigned to the HHT condition will have greater improvements in RQ scores (as measured by the dyadic adjustment scale) than will those in UC. Secondary aims include measuring the impact of the program on relationship quality at 6 months and secondary outcomes, including cardiovascular and cortisol reactivity, inflammatory markers, mental health, quality of life, health behaviors, and cardiovascular risk factors, at 8 weeks and 6 months. We expect greater improvements in all secondary outcomes among HHT participants than in UC participants. This paper describes the study design, objectives and method.

## Method

### Design

The study is a single-centre, RCT with parallel group design. After a baseline assessment, participants are randomized in a 1:1 fashion, using a computer-generated sequence utilizing permuted blocks of 4, 8 and 10 initiated by the institutional methods centre, to the HHT program or to UC. Since sex and participation in CR can have an impact on the study outcomes, randomization is stratified by patient sex (male/female) and participation in the University of Ottawa Heart Institute (UOHI) CR program (yes/no). The trial began in October 2019 and data collection is ongoing. The protocol was approved by our institutional research ethics board (OHSN-REB# 20190101-01H) and all participants provide informed consent. Figure 1 depicts the study design and cohort flow.

**Figure 1 fig1:**
[figure not shown]
Study design and cohort flow.

### Participants

Patients at a large cardiac care hospital in Canada and their partners are approached to participate if they meet the study eligibility criteria, including: (1) being in a romantic relationship of any sexual orientation for at least 1 year; (2) living together for one or more years; (3) the patient having a cardiac event, procedure, or hospitalization in the past 6 months; (4) being 18 years or older; and, (5) being available to participate for 6 months. As a substantial number of participating couples reported high relationship satisfaction and, thereby, likely experience limited benefit from the HHT intervention, in July 2023, another inclusion criterion – one or both partners must score below the satisfied range on relationship quality (i.e., score of <107 on the Dyadic Adjustment Scale (DAS) questionnaire) (Spanier, 1976) - was added as advised by the study biostatistician. Exclusion criteria include: (1) those with any psychiatric or cognitive problems that would impair participation in the HHT program. Staff screen for impairment via chart review. If nothing is documented but a potential participant appears to have these impairments, the study psychologist would determine (either through further chart review or discussion with the research coordinator, referring clinician, or patient) whether participation is appropriate, or (2) planned or active participation in couples’ therapy. Since the HHT program materials were available in English only at the study outset, participants are required to read and understand English. However, the option to complete questionnaires in French or English or speak in their first language during some tasks is possible.

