### Statistical analyses

#### Sample-size calculation

An *a priori* calculation was performed using RQ as measured by the DAS at 8 weeks as the primary outcome. Sample size was derived in 3 steps. First, we examined the standard deviation (SD) of the DAS scores pre-post intervention (SDchange) of pilot patients and partners separately (i.e., HHT pilot data); all SDchange values were close to 10. The consensus of the study investigators and other clinical content experts was to identify a minimum clinically important difference (MCID) based on a small (0.20) to moderate (0.50) Cohen’s effect size. The difference between the HHT and UC groups in the mean change was 3.9 for a small to moderate effect size. This value is close to the commonly used minimum mean change score for the DAS (3.16) (Jacobson and Truax, 1991). Then, we used these values (SDchange = 10; MCID = 3.9) to calculate the sample size with PASS15 sample size software. With 210 couples assigned in a 1:1 fashion to the two groups, we will have 80% power to detect a difference of 3.9 in the change in the DAS between the HHT and UC groups (*α* = 0.05). Nonetheless, we aim to inflate our sample size to account for the design effect of clustering (design effect = 1 + (m-1)*ICC = 1.21 = 254 couples), assuming that our average group size (m) will be 8 couples and our ICC is 0.030. We further increased our sample size target to 304 couples to account for an expected 20% loss to follow-up. As such, we aim to recruit 304 couples but will have sufficient power to detect differences in the primary outcome with 210 couples.

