#### Planned statistical analyses

SPSS and HLM statistical software will be used to analyze the study data. Demographic and clinical variables reported by participants who complete assessments will be compared to those lost to follow-up to verify the representativeness of the cohort. Analyses will be with the intent to treat sample. Research staff record all cases of missing data, including non-retention of participants or withdrawal of consent. Where data are missing, the frequency and reasons for missing data will be recorded. Missing data will be statistically examined for patterns of systematic missingness, and an appropriate missing data strategy will be employed. In situations where data are missing, the data collected up to that point will be used, provided the participant has not withdrawn their consent or requested that the information be removed. For the *primary outcome*, a multilevel analysis of covariance with individuals’ DAS values at 8 weeks as the dependent variable and DAS baseline scores as the covariate at level 1 of the model. The study conditions (HHT vs. UC) to which couples were assigned will be dummy-coded and entered at level 2. To evaluate *secondary outcomes,* a three-level multi-level model for repeated measurements will be utilized. The analysis will include repeated measurements within individuals in Level 1, between-individual variability in Level 2, and couples in Level 3. Within-couple slope variances will be fixed at Level 2 but allowed to vary at Level 3 (Atkins, 2005). A linear parameter will model changes in outcomes from baseline to 8 weeks to 24 weeks. The study condition (HHT vs. UC) will be dummy-coded and modeled as a fixed effect at Level 3. Baseline patient control variables will be entered at Level 2. Binary outcomes will be modeled utilizing a logit link. Improved model fit between nested models will be evaluated using deviance statistics and a chi-square distribution. Effect sizes will be assessed with the pseudo-R squared statistic or Cohen’s d when appropriate. Full maximum likelihood estimation method will be applied for all analyses. For both primary and secondary analyses, we will also conduct stratified analyses for all outcomes by sex (male/female), CR participation (yes/no), and relationship quality (distressed/not distressed on the DAS).

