### Anticipated outcomes

It is expected that participants randomized to HHT intervention will report higher RQ (≥3.9 points on the DAS) and improved secondary outcomes as compared to those in UC.

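### The protocol says many enrolled couples likely gain little, but its claim of sufficient power at 210 couples and its expected pooled difference of 3.9 points were not revisited

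*Protocol article*

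**What the plan says.** The Design section states: "The trial began in October 2019 and data collection is ongoing". For roughly the first three years and nine months (October 2019 to July 2023), couples entered without any DAS criterion. In July 2023, on the biostatistician's advice, the Participants section added the requirement that "one or both partners must score below the satisfied range on relationship quality (i.e., score of <107 on the Dyadic Adjustment Scale (DAS) questionnaire". The reason given is that "a substantial number of participating couples reported high relationship satisfaction and, thereby, likely experience limited benefit from the HHT intervention". No number or share of such couples is reported.

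The sample-size section describes an a priori calculation: "we used these values (SDchange = 10; MCID = 3.9) to calculate the sample size with PASS15 sample size software". It gives 210 couples for 80% power, 254 after a design effect of 1.21, and 304 after allowing for 20% loss. It closes by saying that the trial "will have sufficient power to detect differences in the primary outcome with 210 couples". No revision after July 2023 is described. Under Anticipated outcomes, the HHT group "will report higher RQ (≥3.9 points on the DAS".

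The primary analysis is one intention-to-treat multilevel ANCOVA with baseline DAS as covariate. Additional stratified analyses include one by "relationship quality (distressed/not distressed on the DAS". The text does not say whether this stratum is set for the individual or the couple, and it names no interaction test.

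**The concern.** The eligibility change rests on the judgement that part of the sample already enrolled will respond less. The power statement and the anticipated effect apply to the whole sample, including that part, and read as if the judgement had not been made. The statements fit together only if the remaining couples gain more than 3.9 points.

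If they do not, the pooled primary test has less power than a reader would take from the text. A null pooled result would then be hard to tell apart from the dilution that the protocol itself anticipates. The stratified analysis is the natural place to resolve this, but as described it is not linked to the rule that now defines the target population. That rule concerns the couple (one or both partners below the cut-off). A satisfied partner in an eligible couple would fall in the non-distressed stratum if the stratum were set person by person.

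**Working it through.** **Inputs.** From Sample-size calculation: SD of change 10, difference 3.9, alpha 0.05, 210 couples 1:1, group size 8, ICC 0.030, 20% loss, target 304. Sidedness is not stated; two-sided reproduces the figure, and one-sided would give 164 couples. Assumed, because the documents do not give them: f, the share of satisfied couples in the analysed sample, and r, their effect relative to 3.9.

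**1. The plan's own figure.** n per arm = 2(1.960 + 0.842)² × 10² / 3.9² ≈ 103.2, so 104 per arm and 208 in all. The noncentral t distribution gives 80.3% power at 105 per arm. The stated 210 reproduces.

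**2. 210 couples with the protocol's design effect, no dilution.** 1 + (8 − 1) × 0.030 = 1.21. Effective N = 210 / 1.21 = 173.6. Noncentrality = 3.9 / (10 × √(4/173.6)) = 2.57, which gives 72.4% power.

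**3. The full target, no dilution.** 304 × 0.8 / 1.21 = 201.0 effective couples, which gives 78.6% power.

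**4. Dilution.** If the other couples gain exactly 3.9, the pooled difference is 3.9 × [(1 − f) + f·r]. Power by two-sample t test, SD 10, two-sided 0.05, one score per couple:

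| f | r | Pooled difference | Power, effective N 210 | Power, effective N 201 | Gain needed in other couples for a pooled 3.9 |
|---|---|---|---|---|---|
| 10% | 0.5 | 3.71 | 76.2% | 74.3% | 4.11 |
| 20% | 0.5 | 3.51 | 71.6% | 69.7% | 4.33 |
| 30% | 0.5 | 3.32 | 66.7% | 64.7% | 4.59 |
| 40% | 0.5 | 3.12 | 61.4% | 59.5% | 4.88 |
| 10% | 0 | 3.51 | 71.6% | 69.7% | 4.33 |
| 20% | 0 | 3.12 | 61.4% | 59.5% | 4.88 |
| 30% | 0 | 2.73 | 50.4% | 48.6% | 5.57 |
| 40% | 0 | 2.34 | 39.3% | 37.9% | 6.50 |

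The last column is 3.9 / [(1 − f) + f·r]. An effective N of 210 corresponds to 254 analysed couples (254 / 1.21 ≈ 210), not to 210 analysed couples.

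**The case against.** The strongest reply is that 3.9 is presented as a minimum clinically important difference and the calculation is labelled a priori. Power to detect 3.9 is a conditional statement, and it stays correct for that value whatever the true effect is. This stands. What it does not protect is the expectation that the pooled sample will show at least 3.9, or the unqualified claim at 210.

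Second, limited benefit is not absent benefit, and enrichment after July 2023 may offset the dilution. With f = 30% and r = 0.5, a gain of about 4.6 in the other couples restores 3.9. This is possible, but the document neither states nor argues it.

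Third, the table uses one score per couple, while the planned model uses both partners and adjusts for baseline. If partners' changes correlate 0.5 (an assumption), the SD of the couple mean is 10 × √((1 + 0.5)/2) = 8.66. At f = 20%, 243 analysed couples and design effect 1.21, power is then about 72% (r = 0) or 82% (r = 0.5). On the same assumption, 210 couples with the design effect and no dilution would have about 84%. So the tabulated figures are not the trial's actual power. The protocol's calculation does not use this gain, however, and its claim has to be judged on its own inputs.

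Fourth, baseline DAS is a covariate and distressed/not distressed strata are planned. The covariate reduces variance but leaves the average treatment effect under test unchanged. The strata do help, and a fuller plan may define them; the text shown does not tie them to the entry rule.

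A reader might infer that the protocol concedes these couples will not benefit, or should not have been enrolled. It says neither: they met the criteria in force at the time. A reader might also infer that pooling is wrong or that an enrolment-era term is required. Keeping all randomised couples is correct under intention to treat. An era main effect would not undo dilution.

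**Conclusion.** The point holds as an unreconciled set of statements, not as a demonstrated shortfall in power. The reason given for the July 2023 criterion undercuts the assumption that the pooled sample will show 3.9 points, and neither the power text nor the anticipated effect acknowledges this.

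The size cannot be fixed from the document. At an effective N of 210, power runs from 76% down to 61% (r = 0.5) and from 72% down to 39% (r = 0) as f goes from 10 to 40%. This assumes SD 10, one score per couple and a gain of exactly 3.9 in the other couples. The lower end requires no effect at all in satisfied couples, which is harsher than the protocol's wording.

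The claim that 210 couples suffice fails without any dilution assumption. On the protocol's own design effect, power there is about 72%.

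**What to change.** Keep all randomised couples as the intention-to-treat primary set.

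- **Sample-size calculation:** withdraw the claim of sufficient power at 210. Restate power for the pooled sample, using the share of satisfied couples known to the trial team and a range of effects in them.
- **Anticipated outcomes:** align the expected difference with that restatement, or say why the other couples are expected to gain more than 3.9.
- **Planned statistical analyses:** define the relationship-quality stratum by the current couple-level entry criterion (one or both partners below the DAS cut-off at baseline), applied to couples from before and after the change. Pre-specify the primary model in couples who meet it, with a treatment-by-criterion interaction.

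An enrolment-era factor is optional.

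The cost is wording, one extra model and a less favourable stated power. Baseline DAS is already collected from both partners before randomisation, so selecting on it preserves the randomised comparison. Data collection was ongoing when the article was written; the definition should be fixed before outcome results are seen.
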